## Abstract

**Introduction:**

The incidence of stroke is increasing steadily due to factors such as population aging. Approximately 80% of stroke survivors have motor disorders affecting their daily lives. Repetitive transcranial magnetic stimulation (rTMS) has been reported to maximize functional recovery after stroke along with exercise intervention in upper limb rehabilitation treatment. However, whether rTMS affects the recovery of upper limb function in patients with stroke remains unclear. Therefore, in this trial, we will investigate the efficacy of low-frequency rTMS in patients with subcortical and brainstem ischemic stroke.

**Methods:**

This study has been designed as a multi-center, double-blind, randomized controlled trial to compare the efficacy of low-frequency rTMS over the contralesional M1 with sham stimulation. Overall, 88 participants will be allocated to the intervention or control group in a 1:1 ratio, with stratification according to their initial upper extremity Fugl-Meyer assessment (UE-FMA) score. The participants will receive either 30 min of real rTMS (intervention group) or sham rTMS (control group), followed by 30 min of occupational therapy for 10 consecutive workdays. All the participants will receive the same amount of rehabilitation therapy throughout the intervention period. Evaluations will be performed at baseline (T0), at the end of treatment (T1), and 4 weeks after the end of treatment (T2), including the box and block test (BBT), UE-FMA, Korean version of the Modified Barthel Index, and NIH Stroke Scale scores, Finger tapping test, Brunnstrom stage, modified Ashworth scale, and grip strength. The primary outcome will be the change in the BBT score between T0 and T2.

**Conclusion:**

This study will provide evidence on the efficacy of low-frequency rTMS in motor function recovery of the upper limb in patients with subacute, subcortical, and brainstem ischemic stroke.

**Clinical trial registration:**

ClinicalTrials.gov, identifier [NCT05535504].

## Introduction

1.

Stroke occurs in more than 12 million people worldwide every year, and its incidence is steadily increasing owing to various factors, including population aging (1). Approximately 80% of stroke survivors have motor disorders that affect their daily lives (2). Furthermore, 60–70% of the patients with stroke experience upper extremity motor function damage during hospitalization, and approximately half (33% of all strokes) of them are classified as having severe paralysis. Additionally, 50–70% of stroke survivors suffer paralysis of upper extremity motor function 2–4 years after stroke (3).

Various treatments have been attempted to restore upper limb motor function after stroke, with upper limb rehabilitation treatment, including various physical training approaches (work therapy, muscle strengthening, etc.), currently being applied as a standard treatment for upper limb motor function recovery after stroke (4). These upper-limb rehabilitation treatments induce continuous cortical reconstruction in both hemispheres and promote adaptation to cortical maps, resulting in neuroplasticity after stroke, which benefits functional recovery with longer repetition or intervention periods. However, the extent of recovery of damaged brain tissue and its function using this method is limited. Therefore, many patients have limitations in function due to the aftereffects of stroke, which leads to an increase in social costs (4, 5).

Recently, several non-invasive neuroregulatory intervention studies have reported maximizing functional recovery after stroke in upper limb rehabilitation (5); several studies have reported that repetitive transcranial magnetic stimulation (rTMS) with rehabilitation training such as occupational therapy increases functional recovery (4). Chang et al. (6) investigated the effects of high-frequency rTMS (10 Hz) on the affected hemisphere’s primary motor cortex by comparing it with sham rTMS in patients with subacute stroke who underwent motor training. The results revealed that the group that received the real rTMS showed greater recovery in the sequential finger motor task, indicating the positive impact of rTMS on motor function improvement (6). Di Lazzaro et al. (7) conducted a study comparing the effects of inhibitory theta burst stimulation (iTBS) and sham TBS administered prior to physical therapy in patients with chronic stroke. The results revealed that the iTBS group showed significantly higher scores on the Jebsen-Taylor Test at 3 months post treatment, compared with the sham group (7). rTMS is a treatment method that repetitively stimulates the cerebral nerve area by inducing current to the cerebral cortex, by forming a magnetic field similar to that of Magnetic Resonance Imaging (MRI) in the cerebral cortex. It is a non-invasive and safe method that is widely used not only for patients with stroke but also for neurostimulation in patients with depression, Parkinson’s disease, Huntington’s disease, and cerebral palsy (5).

Representative rTMS protocols include high-frequency rTMS, which is mainly implemented in the ipsilesional primary motor cortex, and low-frequency rTMS, which is mainly implemented in the contralesional M1 (8). Low-frequency rTMS over the contralesional primary motor cortex (M1) has been used to suppress excessive inhibition of ipsilesional M1. That is, it is applied as an attempt to reduce interhemispheric inhibition (IHI) (9). Low frequency rTMS has less impact on motor behavior and reduces risk of seizures in healthy cortical spine systems (8, 10). Therefore, most studies on motor recovery after stroke have applied low-frequency rTMS over the contralesional M1 region.

Research on the effectiveness of rTMS remains controversial. Hsu et al. (11) performed a meta-analysis of 34 existing studies in 2012 and confirmed the significant effects of rTMS on upper limb motor function recovery in patients with stroke. In contrast, Graef et al. (4) investigated the effects of rTMS combined with upper limb training vs. sham rTMS combined with upper limb training on upper limb recovery after stroke in 2016 and concluded that there were no significant differences between groups. Harvey et al. (12) reported a clinical study comparing the effects of rTMS and sham rTMS on the functional recovery of the upper extremities of stroke patients in 2018, and found no difference between the rTMS and sham rTMS groups. Therefore, it is unclear whether rTMS affects the recovery of upper limb function in patients with stroke. Harvey et al. (12) suggested that no significant effect was confirmed because the effect of rTMS may vary depending on the location or severity of the stroke. Graef et al. (4) suggested that the heterogeneity of occupational therapy between studies was the reason why a significant effect of rTMS was not confirmed in the meta-analysis.

Kim et al. (13) conducted a randomized controlled trial to determine the efficacy of low-frequency rTMS on the contralateral M1 combined with occupational therapy in patients with stroke. Although the study did not show a significant difference between the rTMS and sham groups, subgroup analysis based on cortical involvement revealed that low frequency rTMS on contralesional M1 led to improvements in the Brunnstrom stage of hand function in the group without cortical involvement. This result led us to hypothesize that the type and location of stroke may affect the efficacy of rTMS warranting further investigation.

Therefore, a multicenter randomized controlled trial has been designed to confirm the effectiveness of low-frequency rTMS over the contralesional M1 in patients with subcortical and brainstem ischemic stroke.

## Methods

2.

### Study design

2.1.

In this prospective, multi-center, double-blind, randomized sham-controlled, superiority trial, the effectiveness of low-frequency rTMS over the contralesional M1 will be compared to that of sham rTMS in patients who require upper limb rehabilitation due to subcortical and brainstem ischemic stroke.

Patients admitted with acute stroke will be recruited from the rehabilitation ward. Eligibility will be screened by the research team and the patients will be randomly allocated to the intervention group (real rTMS) or control group (sham rTMS) in a 1:1 ratio, with stratification into two subgroups according to the baseline Upper Extremities Fugl-Meyer Assessment (UE-FMA) score. The baseline evaluation (T0) will be performed by a blinded evaluator after group allocation. All participants will receive 30 min of intervention (real rTMS in the intervention group and sham rTMS in the control group), accompanied by 30 min of occupational therapy (OT) after the intervention. The intervention will be provided to participants for 10 consecutive working days. All participants will receive the same amount of occupational and physical therapy (PT) consisting of two sessions of 30-min OT and PT daily during this period. The evaluation will be performed at the end of the intervention period (T1) and 4 weeks after the end of the intervention (T2). The doses of OT and PT will be monitored and documented by the patient/caregiver at T1 and T2. An overview of the study design and process is shown in Figure 1.

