### Participants and recruitment

2.2.

In this study, the authors will enroll 88 adult participants, from two institutions recruiting 44 participants each: Seoul National University Bundang Hospital (Gyeonggi-do, Republic of Korea) and Chungnam National University Hospital (Daejeon, Republic of Korea).

The inclusion criteria are as follows: (a) between the ages of 19 and under 80, (b) within 90 days from first subcortical or brainstem ischemic stroke confirmed by Computed Tomography (CT) or Magnetic Resonance Image (MRI) (13), (c) UE-FMA score exceeding 15 points (14), and (d) Korean version of Mini Mental Status Exam (K-MMSE) score of 15 or higher. The exclusion criteria are as follows: (a) diagnosis of a cerebellar stroke, (b) history of cerebrovascular surgery, (c) wrist score of less than 1 and hand score of less than 1 (13), (d) history of psychiatric or neurological disease before stroke onset, (e) inability to undergo rehabilitation treatment for other reasons, such as medical problems, and (f) history of epilepsy or seizure disorder. The detailed inclusion and exclusion criteria are listed in Table 1.

**Table 1 tab1:** Major inclusion and exclusion criteria.

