### Randomization and blinding

2.3.

A list of random assignments will be prepared by a statistician who is independent of the research team. Within each institution, the participants will be stratified into two subgroups based on a baseline UE-FMA score of 28 using a stratified block randomization method with blocks of size 2 within each stratum, and the assignment ratio of the intervention and control groups will be maintained at 1:1. A random assignment list will be generated using SPSS version 23.0(IBM Corp., Armonk, NY, United States). The block size and seed number used will be randomly selected by a statistician responsible for the random assignment. Random assignments will be stored in opaque envelopes for each participant and delivered to the coordinator at the start of the intervention.

This clinical trial will be performed in a double (participant and evaluator) blind-fold manner, and the therapists who perform the treatment will also be blinded throughout the study. Owing to the nature of this clinical trial, the investigator who will perform rTMS will not be blinded to the assigned group.

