#### Primary outcome measure

2.5.1.

Primary outcome is the amount of change in the number of Box and Block Test (BBT) (17) at T2 compared to that at T0 (3, 5, 13, 18). The BBT is a manual dexterity test that has been used to evaluate physically disabled individuals. The BBT consists of a partition and wooden box divided into two compartments containing 150 blocks. Participants will be asked to move as much as possible, one at a time, from one compartment of the box to another of the same size, within 60 s. The BBT score is the number of blocks the participant has moved (17).

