**Secondary outcome measures**			
Upper extremity FMA	√	√	√
K-MBI	√	√	√
NIHSS	√	√	√
Finger Tapping Test	√	√	√
Brunnstrom stage	√	√	√
Modified Ashworth scale	√	√	√
Grip strength	√	√	√

EOT, end-of-treatment; FMA, Fugl-Meyer Assessment; K-MBI, Korean version of the Modified Barthel Index; NIHSS, National Institutes of Health Stroke Scale.

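### T0, the source of the primary outcome's reference value and covariate, is scheduled after allocation, and the article does not say which UE-FMA sets the randomisation stratum

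*Protocol article*

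**What the plan says.** Two consecutive statements in section 2.1 (Study design) set the order. Patients are allocated 1:1 "with stratification into two subgroups according to the baseline Upper Extremities Fugl-Meyer Assessment (UE-FMA) score", and then: "The baseline evaluation (T0) will be performed by a blinded evaluator after group allocation".

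Section 2.3 (Randomization and blinding) again uses the word baseline for the stratifier: "the participants will be stratified into two subgroups based on a baseline UE-FMA score of 28". On release of the assignment it says: "Random assignments will be stored in opaque envelopes for each participant and delivered to the coordinator at the start of the intervention". It gives blocks of size 2 within each stratum, blinds participants, evaluator and therapists, and leaves the rTMS operator unblinded.

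Table 2 (section 2.5.2) lists "Upper extremity FMA" and the BBT at T0, T1 and T2, with no earlier column. Section 2.2 makes "UE-FMA score exceeding 15 points" an inclusion criterion.

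Under section 2.5.1 the primary outcome is the BBT change from T0 to T2. Under section 2.8.3 the ANCOVA adjusts for BBT at T0 and for the stratification variable (UE-FMA below 28 or not), among other terms.

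**The concern.** Two things follow from the stated order.

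First, a score measured after allocation cannot decide the stratum in which the patient is allocated. Some UE-FMA must come earlier, because eligibility depends on it, but the article neither names that value nor links it to the stratum. If a screening value and a T0 value both exist, they can fall on opposite sides of 28. The stratum in the model could then differ from the stratum used to randomise.

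Second, a baseline recorded before allocation is independent of treatment assignment by design. A baseline recorded afterwards is independent only if nobody who can influence the measurement knows or guesses the assignment. T0 BBT enters the primary analysis twice, as the value subtracted and as a covariate. It is a 60-second performance test, so effort and encouragement can affect it. The same order applies to every secondary change score that starts from T0.

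**Working it through.** **The sequence, place by place**

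- Section 2.1: screening, then allocation stratified on baseline UE-FMA, then the T0 evaluation.
- Section 2.2: UE-FMA above 15, plus wrist and hand sub-scores, needed for eligibility. A UE-FMA therefore precedes allocation.
- Section 2.8.2: names items collected at screening, among them Brunnstrom stage and K-MMSE. UE-FMA is not named, but the list is not presented as complete.
- Table 2: UE-FMA first appears at T0.
- Section 2.3: the envelope reaches the coordinator at the start of the intervention. This may put disclosure after T0 even if the allocation is formally made before it.

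Taken together, a workable sequence exists (screening UE-FMA, stratum, allocation, T0, treatment), but the text does not state it. The order of allocation, disclosure and T0 is left open.

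**The plan's own figure**

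Inputs from section 2.6: difference 17.40 − 10.90 = 6.50, SD 10.30, alpha 5%, power 80%. Sidedness is not stated; two-sided is assumed here.

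n per group = 2 × (1.960 + 0.842)² × 10.30² / 6.50² = 39.4, rounded up to 40. Adding 10% gives 44 per group, 88 in total. The sample size reproduces, and this point does not change it.

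**What a T0 error would do**

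Adjusting the change score for T0 is the same as regressing T2 on arm and T0 with slope b. Suppose observed T0 equals true T0 plus an error d in one arm only. The within-arm slope is unchanged, and the estimated arm difference moves by b × d in absolute size. Understating T0 in the rTMS arm favours rTMS; understating it in the sham arm works against rTMS. A chance imbalance in true T0 is adjusted for and is not carried into the estimate.

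The documents give neither d nor b. Both are assumed:

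- d = 1, b = 0.8: 0.8 blocks; 0.8 / 6.50 = 12% of the planned effect.
- d = 2, b = 1.0: 2.0 blocks; 2.0 / 6.50 = 31%.

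To show what such shifts mean for the test, take b = 1 (a plain change-score comparison), 40 per group and SD 10.30. The standard error is 10.30 × √(2/40) = 2.30 blocks.

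| Assumed shift (blocks) | Two-sided type I error if it favours rTMS | Power if it works against rTMS |
|---|---|---|
| 0 | 0.05 | 0.81 |
| 0.5 | 0.055 | 0.74 |
| 1 | 0.072 | 0.67 |
| 2 | 0.140 | 0.50 |

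Under ANCOVA with b below 1 the bias is smaller, and the standard error also differs, so the table does not carry over exactly.

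**The case against.** The strongest reply is that the wording is loose and the design is sound. Screening precedes allocation, the eligibility rule guarantees a pre-allocation UE-FMA, and the abstract and Discussion call the stratifier the initial score. Brunnstrom stage is listed both at screening and at T0, so measuring a scale twice is already part of the plan. Table 2 lists outcome measures and is not a full visit schedule. The stratification term in section 2.8.3 is most plainly the randomisation stratum. The T0 evaluator, participants and therapists are blinded, assignments sit in opaque envelopes, and T0 precedes treatment. A failure of blinding would also affect T1 and T2, which moving T0 does not cure.

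Most of this stands, and it rules out four stronger readings that a reader might infer:

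- That the sequence is impossible. It is not: a screening UE-FMA can set the stratum. The article just does not say so.
- That any arm difference at T0 passes into the result. ANCOVA adjusts for genuine chance imbalance; only error that differs by arm is transmitted.
- That a bias of 12–31% has been shown. Those percentages rest wholly on an assumed error and an assumed slope.
- That patients who leave between allocation and T0 are lost to the ANCOVA for lack of a baseline. They are untreated, and section 2.8.4.1 already places them outside the full analysis set.

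The reply does not justify the order itself. Section 2.1 states expressly that T0 follows allocation, and nothing in the article says why. The envelope sentence may mean that disclosure comes after T0, but it does not settle this. With blocks of 2, anyone who knows the first assignment of a pair knows the second, and the unblinded rTMS operator has that knowledge.

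**Conclusion.** The point holds as a defect of stated sequence and definition. The text is certain on two matters: T0 follows allocation, and the stratifier is called baseline UE-FMA without saying which measurement is meant. The consequence for the estimate is conditional. It needs knowledge or a guess of the assignment to reach the T0 assessment and to affect it differently by arm, and the stated blinding makes that a risk only. If it happened, the bias would be the T0 error times the slope: 0.8–2.0 blocks under the assumed 1–2 block error and 0.8–1.0 slope. How often a screening and a T0 UE-FMA would straddle 28 cannot be estimated from the article. The change is worth making because T0 BBT underlies the primary endpoint and the reliance on concealment at T0 is avoidable.

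**What to change.** - In section 2.1, state that T0 BBT and UE-FMA are completed and recorded in the eCRF before the assignment is made or the envelope opened.
- In section 2.3, name one pre-allocation UE-FMA, either the T0 value under the new order or a screening value, as the one that sets the stratum.
- In sections 2.8.3 and 2.8.4, state that the ANCOVA uses that same randomisation stratum and does not re-derive it.
- Align section 2.5.2 and Table 2 with this, adding a screening UE-FMA entry if that value is the stratifier.

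Naming a screening UE-FMA would by itself settle the stratum, but T0 BBT should still be recorded before allocation. The new order closes the route by which a disclosed assignment could reach T0. It does not stop an assignment being predicted from blocks of 2, which section 2.3 must deal with separately.

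The cost is a reordering of existing steps and a few lines of text, with no apparent extra visit or assessment. The article does not give the interval between screening, allocation and T0, so the sites should confirm that the order is practicable.

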**Figure 1 fig1:**
[figure not shown]
Experimental design. Participants will receive 30-min of daily real or sham repetitive transcranial magnetic stimulations (rTMS) over a period of 10 consecutive workdays. Task-based occupational therapy (OT) of 30 min for upper limb recovery will be applied within 10 min after rTMS session. Assessments will be performed at baseline (T0), end of treatment (T1), and 1 month (T2) after the last session of rTMS.

### Participants and recruitment

2.2.

In this study, the authors will enroll 88 adult participants, from two institutions recruiting 44 participants each: Seoul National University Bundang Hospital (Gyeonggi-do, Republic of Korea) and Chungnam National University Hospital (Daejeon, Republic of Korea).

The inclusion criteria are as follows: (a) between the ages of 19 and under 80, (b) within 90 days from first subcortical or brainstem ischemic stroke confirmed by Computed Tomography (CT) or Magnetic Resonance Image (MRI) (13), (c) UE-FMA score exceeding 15 points (14), and (d) Korean version of Mini Mental Status Exam (K-MMSE) score of 15 or higher. The exclusion criteria are as follows: (a) diagnosis of a cerebellar stroke, (b) history of cerebrovascular surgery, (c) wrist score of less than 1 and hand score of less than 1 (13), (d) history of psychiatric or neurological disease before stroke onset, (e) inability to undergo rehabilitation treatment for other reasons, such as medical problems, and (f) history of epilepsy or seizure disorder. The detailed inclusion and exclusion criteria are listed in Table 1.

**Table 1 tab1:** Major inclusion and exclusion criteria.

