#### Analysis of primary outcome

2.8.3.

Descriptive statistics (number of participants, mean, standard deviation, median, minimum, and maximum) of the BBT values at T0 and T2 and the degree of BBT change between T0 and T2 will be presented by group. The statistical significance of BBT changes between groups will be confirmed by analysis of covariance (ANCOVA) with the number of BBTs at T0 and stratified variables (depending on whether the UE-FMA score is less than 28 points) and occupational therapy dosage between T1 and T2 as covariates. Additionally, in the subgroup analysis, the location of stroke lesions will also be included as a covariate in the ANCOVA. All statistical analysis will be performed with significance level of 0.05.

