## Discussion

3.

This study was designed as a multi-center, double-blind, randomized sham-controlled trial that aims to confirm the efficacy of low-frequency contralesional rTMS in the recovery of upper limb motor function in patients with subcortical or brainstem ischemic stroke. To ensure the rigor of the investigation, the participants will be stratified into two subgroups based on their initial severity. Moreover, the amount of OT and PT will be the same in the intervention and control groups during the intervention period, and the amount of total therapy will be recorded throughout the trial. By controlling and recording the potential cofounders of the motor recovery after stroke, the study results are anticipated to report high-quality evidence on the effectiveness of rTMS on motor recovery after stroke.

In this study, among various rTMS protocols, low frequency rTMS over the contralesional M1 will be applied in attempts to normalize imbalance of IHI by suppressing the over-inhibition of contralesional M1 toward ipsilesional M1 (9). In previous studies, low-frequency rTMS was often chosen over high-frequency rTMS because of the low risk of seizures in the healthy corticospinal system and its minimal effect on motor behavior (8, 10). However, previous results regarding the efficacy of low-frequency rTMS over the contralesional M1 for motor recovery in patients with acute and subacute stroke remain inconsistent. Khedr et al. (24) reported that low-frequency rTMS is more advantageous in recovering upper extremity function after stroke compared to high-frequency rTMS. Dafotakis et al. (29) also reported the possible beneficial effects of low-frequency rTMS on hand function recovery in patients with acute and subacute subcortical stroke. In contrast, other studies have reported no significant beneficial effects of low-frequency rTMS compared with sham rTMS (30, 31). In a meta-analysis, Hsu et al. (11) confirmed the effect of low-frequency rTMS on the recovery of upper extremity function in patients with stroke and reiterated the notion that post-stroke hemisphere competition is altered and that this imbalance can be resolved by reducing the cortical excitability of unaffected hemispheres through low-frequency rTMS.

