Recently, it has been reported that the location of stroke lesions is a key factor in the efficacy of rTMS in upper limb motor recovery. Kim et al. (13) confirmed that the recovery of the upper extremities was significant only in patients without cortical invasion. Ameli et al. demonstrated that high-frequency rTMS on the ipsilesional M1 was effective only in patients with subcortical stroke and not in patients with additional cortical stroke (32). Nowak et al. (33) conducted cross-over investigation in patients with subacute subcortical stroke and found that application of rTMS to the contralesional M1 improved the kinematics of finger and grasp movements in the affected hand. Based on these findings, the target population of this trial was narrowed down to patients with subacute subcortical or brainstem ischemic stroke. Previous studies have explained possible reasons for the better effects of rTMS in patients with stroke without cortical involvement. First, the expected increase in cortical activity in the ipsilesional M1 through rTMS is inefficient in propagating to other nodes of the motor network for motor recovery, as there is a structural or functional disconnection in stroke that invades the cortex (32, 34). Second, in the cortical brainstem, GABAergic intracortical inhibition is greater, and concurrent downregulation of GABA receptors in both hemispheres has been identified, which may be associated with the reduced effects of rTMS (13).

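### Entry is open at any time up to 90 days after stroke, but time since stroke is neither stratified nor in the listed ANCOVA covariates: a free gain in precision is left unused

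*Protocol article*

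**What the plan says.** **Entry.** Section 2.2 admits patients "within 90 days from first subcortical or brainstem ischemic stroke confirmed by Computed Tomography (CT) or Magnetic Resonance Image (MRI"). Table 1 repeats the 90-day limit. Neither gives a minimum time since onset. Section 2.1 adds: "Patients admitted with acute stroke will be recruited from the rehabilitation ward".

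**Randomization.** Section 2.3: "Within each institution, the participants will be stratified into two subgroups based on a baseline UE-FMA score of 28". No other stratification factor is named.

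**Analysis.** Section 2.8.3 names this model for the primary outcome, BBT change from T0 to T2: "analysis of covariance (ANCOVA) with the number of BBTs at T0 and stratified variables (depending on whether the UE-FMA score is less than 28 points"). Its covariate list ends: "occupational therapy dosage between T1 and T2 as covariates". Lesion location enters only in the subgroup analysis. The ANCOVAs in section 2.8.4 use the same kind of list. Time since stroke appears in none of them.

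**Description of the population.** The Discussion says that "the target population of this trial was narrowed down to patients with subacute subcortical or brainstem ischemic stroke". The conclusion of the Abstract also calls the patients subacute; the main Conclusion (section 4) does not use the word.

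**The concern.** The outcome is a change over roughly six weeks (10 working days of treatment plus 4 weeks), in patients who may start at any point in a 90-day window. Two patients with the same baseline BBT may be at quite different stages of recovery. If the expected gain depends on that stage, time since stroke adds spread to the outcome which the planned model cannot remove unless baseline BBT and the two-level UE-FMA factor happen to capture it.

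Section 2.6 shows that change without real stimulation is both large and variable: 10.90 blocks with SD 10.30 in the sham subjects of the previous study. That makes prognostic covariates worth considering.

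Two things are at stake. One is the width of the confidence interval. The other is what happens if the arms turn out to differ visibly in time since stroke: without a prespecified covariate, any adjustment would be post hoc and open to challenge. This cannot be put down to detail that an article leaves out, because the covariates are listed by name and the list fixes the model without this variable.

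**Working it through.** **1. Reproduce the plan's figure.** Inputs from section 2.6: difference 17.40 − 10.90 = 6.50, SD 10.30, significance level 5%, power 80%. Two-sided testing is inferred, since the one-sided formula gives 32.

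n per group = 2 × (1.960 + 0.842)² × 10.30² / 6.50² = 39.4, so 40, as stated. With 44 per group after 10% inflation, the total is 88, as stated. Power of a two-sample t-test with 40 per group is 79.6%.

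**2. Precision before adjustment.** SE of the difference = 10.30 × √(2/40) = 2.30 blocks. 95% half-width = 1.96 × 2.30 = 4.5 blocks. Chance imbalance in every unadjusted factor, time since stroke included, is already inside this interval.

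**3. Precision after adjustment.** Let R² be the share of the remaining variance that time since stroke explains beyond baseline BBT, UE-FMA stratum and the other planned covariates. Then residual SD = 10.30 × √(1 − R²), and the half-width shrinks by the factor √(1 − R²). Power is from the t-test at a difference of 6.50 with 40 per group and one degree of freedom fewer. The documents give no R²; the values below are assumptions.

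| R² (assumed) | Residual SD | 95% half-width | Reduction | Power |
|---|---|---|---|---|
| 0 (plan) | 10.30 | 4.51 | – | 79.6% |
| 0.01 | 10.25 | 4.49 | 0.5% | 80.0% |
| 0.05 | 10.04 | 4.40 | 2.5% | 81.6% |
| 0.10 | 9.77 | 4.28 | 5.1% | 83.6% |
| 0.20 | 9.21 | 4.04 | 10.6% | 87.6% |

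The starting SD of 10.30 is that of the raw change. The planned ANCOVA will already leave a smaller residual SD, which the documents do not give. The percentage reductions carry over to that SD; the absolute half-widths and powers are illustrations.

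**4. How far the arms could differ by chance.** This depends on how entry times are spread, which is also not given. With 40 per arm:

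- Uniform over 0 to 90 days (assumed): SD = 90/√12 = 26.0 days; SE of the difference in means = 26.0 × √(2/40) = 5.8 days; 95% range about ±11 days.
- Uniform over 10 to 40 days (assumed, if ward recruitment clusters entry): SD = 30/√12 = 8.7 days; SE 1.9 days; 95% range about ±4 days.

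**5. How R² depends on the assumptions.** Suppose gain falls by b blocks per day of delay and nothing else absorbs this. Then R² = (b × SD of days / 10.30)².

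- At b = 0.10: (0.10 × 26.0 / 10.30)² = 0.06 for the wide spread, and 0.007 for the clustered one.
- At b = 0.20: 0.25 and 0.03.

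These are upper figures for each pair of assumptions, because baseline BBT and the UE-FMA stratum may absorb part of the effect. The benefit therefore runs from negligible to useful, and the documents do not say where in that range the trial lies.

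**The case against.** The strongest reply is that nothing here is an error. Randomization, stratified by site and severity, gives an unbiased estimate and a valid test whichever covariates are named. The planning SD comes from the same previous study that section 2.2 cites for the 90-day criterion. If that study used a similar window (inferred, not stated), this noise is already in the 10.30 and so in the 40 per group. Slope and spread are both unknown, the planned covariates may capture part of the effect, and recruitment on a rehabilitation ward may make very early entry uncommon. All of this stands, and it limits the point to efficiency.

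It also rules out some stronger readings that a reader might infer:

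- *That an rTMS effect could not be told apart from earlier enrolment in one arm.* The confidence interval already allows for chance imbalance; there is no systematic confounding.
- *That spontaneous recovery makes up most of the expected 17.40-block gain.* The 10.90 blocks are the whole gain under sham stimulation, and section 2.6 does not divide them between spontaneous recovery, rehabilitation and practice.
- *That the Discussion's phrase "By controlling and recording the potential cofounders of the motor recovery after stroke" is contradicted.* It follows sentences on severity stratification and on equal, recorded therapy, and need not claim control of every prognostic factor.

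What the reply does not meet is the choice of covariates itself. The variable is fixed before treatment, must be known for eligibility, and is a plausible predictor of change; leaving it out of a named list has no stated reason.

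**Conclusion.** The point holds as a worthwhile improvement, not as a flaw that endangers validity. The entry window has no lower limit, and time since stroke is absent from both the stratification and the listed ANCOVA covariates. The cost is precision and a prespecified answer to any chance imbalance. The size is uncertain: a half-width 0.5% to 11% narrower, and power between about 80% and 88%, for an assumed additional R² of 0.01 to 0.20. At the low end the gain is negligible. The sample size needs no change, and it would be wrong to read this as a power shortfall.

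A separate, smaller matter of wording also holds. The Abstract's conclusion and the Discussion call the population subacute, whereas section 2.1 recruits patients admitted with acute stroke and section 2.2 and Table 1 set no lower limit. The Discussion itself uses acute and subacute as distinct terms when it describes earlier trials. One might infer that a minimum time since onset ought to be added, but the documents do not define *subacute*, so they support only that the passages be reconciled.

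**What to change.** In sections 2.8.3 and 2.8.4, prespecify days from stroke onset to randomization (or to T0, with one of the two fixed in advance) as a continuous baseline covariate in the ANCOVAs, before unblinding. This takes one sentence and one degree of freedom. It needs no new data, since the 90-day criterion already requires the interval to be established, and it does not affect recruitment. A further stratification factor is not needed with 88 patients already divided by institution and UE-FMA.

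Separately, reconcile the word *subacute* in the Abstract and Discussion with sections 2.1, 2.2 and Table 1, for example by describing the population as patients within 90 days of stroke. That is an edit to the description and leaves eligibility as it is.
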